PITCH-trained HCWs will have an improved sense of competence in providing care, improved dementia knowledge, and reduced carer burden at 6 months, compared with HCWs not trained in PITCH.Clients of PITCH-trained HCWs will report a better experience with their home care service, improved quality of life and health, and exhibit fewer behaviours of concern at 6 months, compared with clients of HCWs not trained in PITCH.Family carers of clients of PITCH-trained HCWs will have reduced carer burden and reduced depressive symptoms at 6 months, compared with family carers of clients with HCWs not trained in PITCH.Clients with usual care will have fewer total days before an all-cause transition from the home event (such as admission to residential care) or greater client total number of transitions from home to hospital or other facilities, compared with clients of PITCH-trained HCWs.PITCH is effective compared to control in terms of quality-adjusted life years as measured by economic evaluation.

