### Sample size

For the primary outcome measure (SCIDS), at 80% power, two-tailed 5% significance level, 12 clusters with 15 HCWs per cluster, will detect a treatment effect size of 0.522 in the treatment group compared with controls. With a 20% drop-out rate, sample size is estimated at 216 HCWs. All eligible clients serviced by these HCWs are invited to participate in the study (approximately 108 participants). The family carers of participating clients are also invited to participate in the study (approximately 108 participants).

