### Randomisation

HCWs are clustered according to the home care provider service region. Each cluster is randomly allocated to the study arms (the intervention or control groups) with block randomisation. The randomisation is conducted using online random number generators in the presence of an independent research staff member who is not employed in the study.

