### Statistics and data analysis

Baseline variables will be fully described using descriptive statistics. The primary (sense of competency) and secondary (dementia knowledge, attitudes, work strain) outcomes for HCWs will be analysed using linear mixed models or generalised linear mixed models (depending on the data distribution and extent of unequal cluster sizes). Secondary outcomes for clients living with dementia and family carers (social care, client experience, health-related quality of life, neuropsychiatric symptoms, disability, carer role strain, dyadic relationship) will be compared pre versus post intervention periods using linear mixed models or generalised linear mixed models. Time and intervention will be represented in these models as fixed effects, whilst cluster and participants will be represented as random effects.

All-cause client transition from the home will analysed using survival analysis, employing Cox proportional hazards modelling and Kaplan-Meier survival curves. Clients of HCWs who did and did not receive PITCH training will be compared using Log rank tests. A prospective economic evaluation will be used to inform the cost-effectiveness of the PITCH program. Incremental costs will be estimated relative to the controls. Quality of life measures will be used to estimate a quality-adjusted life year (QALY) profile for participants. This will be used to estimate the cost per QALY. Statistical uncertainty and sensitivity analyses will be included with these results. Intention-to-treat methods will be used to account for missing data. For missing data, based on the pattern of missingness, we will use either multiple imputation techniques, selection, or pattern mixture models, in consultation with a statistician.

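### The log-rank comparison of transition from home ignores the randomisation of whole service regions, and no cluster term is stated for the accompanying Cox model

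*Protocol article*

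**What the plan says.** The Randomisation section defines the clusters, "HCWs are clustered according to the home care provider service region", and makes them the unit of allocation: "Each cluster is randomly allocated to the study arms (the intervention or control groups) with block randomisation".

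The Statistics and data analysis section first assigns linear or generalised linear mixed models to the questionnaire outcomes of HCWs, clients and family carers. It closes that paragraph with: "Time and intervention will be represented in these models as fixed effects, whilst cluster and participants will be represented as random effects".

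A new paragraph then covers the time-to-event outcome: "All-cause client transition from the home will analysed using survival analysis, employing Cox proportional hazards modelling and Kaplan-Meier survival curves". The group comparison follows: "Clients of HCWs who did and did not receive PITCH training will be compared using Log rank tests". Neither sentence mentions clusters.

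The outcome appears under Other outcomes, but it tests the fourth hypothesis in the Background: "Clients with usual care will have fewer total days before an all-cause transition from the home event".

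**The concern.** The cluster random effect is tied to the mixed models in both grammar and content. It is paired with a participant random effect, which suits repeated questionnaire scores. The survival paragraph stands apart and names a test which, as ordinarily run, treats every client as an independent observation.

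Clients in one region share a provider and a care workforce. The Discussion also describes state rules and provider policies during the pandemic. Correlated transition times within regions are therefore plausible.

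If they are correlated, the ordinary test understates the variance of the comparison. A difference between a few regions could then be reported as training keeping people at home.

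**Working it through.** **1. Reproduce the plan's own figure.** The Sample size section covers only the primary outcome: 12 clusters of 15 HCWs, "at 80% power, two-tailed 5% significance level", detectable effect size 0.522, and 216 HCWs after 20% drop-out.
- Without clustering, 12 × 15 = 180, or 90 per arm. The detectable effect is (1.960 + 0.842) × √(2/90) = 0.418.
- The design effect implied by 0.522 is (0.522/0.418)² = 1.56 (from unrounded values).
- Treated as a two-arm parallel cluster comparison, 1 + 14 × ICC = 1.56 gives an ICC of about 0.04. The article does not state this value.
- 180 × 1.2 = 216, so the stated total is reproduced.

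The sponsor therefore appears to have allowed for clustering among HCWs. No event count, hazard ratio or ICC is given for the transition outcome.

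**2. Direction of the contrast.** By the Abstract, the intervention group is trained after baseline and the control group 6 months later. In the first 6 months, trained versus untrained is a pure between-cluster contrast. Afterwards every cluster is trained. The two-sequence layout therefore supplies no concurrent within-cluster contrast to remove differences between regions.

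**3. Formula check.** About 108 clients are expected (Sample size). The article is not consistent on the number of clusters: 18 (Abstract), groups of 8, so 16 if there are two groups (Fig. 1 caption), and 12 (Sample size). This gives m = 6, 6.75 or 9 clients per cluster. With DE = 1 + (m − 1) × ICC, the true size of a nominal 5% test is 2 × (1 − Φ(1.96/√DE)), and a valid interval is √DE times as wide. The ICCs are assumptions.

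| Clusters | ICC | DE | True size | Width factor |
|---|---|---|---|---|
| 18 | 0.02 | 1.10 | 6.2% | 1.05 |
| 18 | 0.04 | 1.20 | 7.4% | 1.10 |
| 18 | 0.10 | 1.50 | 11.0% | 1.22 |
| 16 | 0.04 | 1.23 | 7.7% | 1.11 |
| 12 | 0.02 | 1.16 | 6.9% | 1.08 |
| 12 | 0.04 | 1.32 | 8.8% | 1.15 |
| 12 | 0.10 | 1.80 | 14.4% | 1.34 |

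Unequal cluster sizes add to this: DE = 1 + ((1 + CV²)m − 1) × ICC. At ICC 0.05 and CV 0.6, DE is 1.36 with 18 clusters (true size 9.3%) and 1.56 with 12 (11.7%).

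**4. Simulation of the ordinary log-rank test with no true effect.** Two independent set-ups were used, each with 108 clients and half the clusters trained.
- *Gamma frailty*, 30% event probability over 6 months, cluster-size CV 0 or 0.6, 4,000 runs per scenario. At ICC 0 the test rejected in 5.0% to 5.7% of runs. Over ICC 0.02 to 0.10 it rejected in 6.0% to 13.5% (18 clusters) and 6.8% to 18.0% (12 clusters).
- *Log-normal frailty*, event probability 20% or 40%, equal clusters, 8,000 runs per scenario. With no variation between clusters it rejected in 4.5% to 5.2% of runs. With a log-hazard SD of 0.3 to 0.7 it rejected in 6.2% to 15.0% (18 clusters) and 6.9% to 20.0% (12 clusters).

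In the gamma set-up, a permutation test that re-allocates whole clusters rejected in 4.5% to 5.4% of runs in every clustered scenario.

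**The case against.** A reader might infer that the Cox model also treats clients as independent, and that its hazard-ratio intervals are therefore too narrow. The article does not say so. It says only "employing Cox proportional hazards modelling and Kaplan-Meier survival curves" and gives no variance estimator, frailty term or exposure coding. This is a condensed article, and Trial status refers to a full protocol (version 8) that is not shown. A shared frailty or robust variance may be specified there, and the authors plainly had clustering in mind for their other models. This objection stands: for the Cox model the point is conditional and calls for clarification.

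It does not rescue the log-rank test, which is named as the group comparison. Run as written, it is an individual-level test of a between-cluster contrast.

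Other points that stand in part:
- The size depends on assumed ICCs and event rates. At ICC 0.02 with 18 clusters the simulated error can be as low as 6.0%, close to the 5.0% to 5.7% seen with no clustering. The 18.0% figure needs 12 clusters, ICC 0.10 and unequal cluster sizes together.
- The simulations used simple half-and-half allocation. The article mentions blocks without naming a blocking factor. If that factor were provider or state, it would balance part of the variation between regions, but not necessarily all of it.
- The outcome ranks below the primary and secondary outcomes, and no power claim rests on it.

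**Conclusion.** The point holds for the log-rank test. It does not respect the cluster randomisation, and its type I error exceeds 5% whenever transition hazards vary between regions. With 108 clients, an assumed 30% event probability and assumed ICCs of 0.02 to 0.10, the error is about 6% to 14% with 18 clusters and 7% to 18% with 12. At ICC 0.04, borrowed from the HCW calculation as an illustration, the formula gives 7.4% to 8.8%.

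For the Cox model the conclusion is conditional. If hazards vary between regions and the full plan adds no cluster term, a valid interval at ICC 0.04 would be 1.10 to 1.15 times as wide as the naive one. The document does not support the unconditional claim that the intervals are too narrow.

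The matter deserves correction because a stated hypothesis rests on this comparison. The primary HCW model already carries a cluster random effect and is unaffected.

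**What to change.** In the survival paragraph of Statistics and data analysis:
- Replace the ordinary log-rank p-value with one cluster-aware test. One option is the log-rank statistic referred to its permutation distribution over the cluster allocations, restricted to those the blocking allowed.
- State that the Cox model carries either a cluster frailty or a cluster-robust variance, with a correction for the small number of clusters. One method, chosen in advance, is enough.
- Keep the Kaplan-Meier curves as description, without a p-value or interval that assumes independent clients.

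If the full plan already specifies this, one clarifying sentence is enough.

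The cost is wording and a few lines of code, with no new data. The downside is a wider interval and lower apparent power for this outcome. Blocking also limits how small a permutation p-value can be. For example, with 12 clusters in assumed blocks of two there are 2⁶ = 64 allocations, so the smallest two-sided p-value is 2/64 = 0.031. The block structure should therefore be checked before the method is fixed.

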**Methods:**

This study is a pragmatic stepped-wedge cluster-randomised controlled trial (SW-CRT). Home care workers (HCWs) from seven home care service providers are grouped into 18 geographical clusters. Clusters are randomly assigned to intervention or control groups. The intervention group receives 7 h of a dementia education and upskilling programme (Promoting Independence Through quality dementia Care at Home [PITCH]) after baseline measures. The control group receives PITCH training 6 months after baseline measures. This approach will ensure that all participants are offered the program. Home care clients living with dementia are also invited to participate, as well as their family carers. The primary outcome measure is HCWs’ sense of competence in dementia care provision.

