## Methods/design

### Trial design

This pragmatic stepped-wedge cluster-randomised controlled trial (SW-CRT) investigates the effectiveness of the PITCH training programme delivered to paid HCWs in improving their competency and dementia knowledge, overall family carers’ wellbeing and clients’ quality of life, and cost-effectiveness. The study participants are clients living with dementia, family carers, and HCWs.

Consistent with the stepped-wedge design, clusters of participants undertake PITCH training (the intervention) sequentially over time and, once their training is completed, will remain exposed to the intervention for the duration of the study. Every cluster begins in the control condition and eventually receives the intervention, with crossover determined randomly, ensuring eventual participation of all groups for ethical reasons. The study is conducted at six home care service providers, with each provider potentially contributing more than one cluster.

This SW-CRT is an interventional study for HCWs as they receive PITCH training, but a non-interventional study for the clients and family carers (no direct intervention treatment is given to clients). HCWs are randomly allocated to either the intervention groups that receive PITCH training at period 2 or the control groups that receives PITCH training at period 3. All participants are monitored throughout the SW-CRT and outcomes for all participants are assessed at three time periods: period 1 (baseline), period 2 (at 6 months), and period 3 (at 12 months). See Fig. 1.

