### Intervention Procedures

The PITCH training programme was co-designed with HCWs and managers, people with dementia and their family carers [see [17, 18] for further details on the development of the PITCH program]. The content was specifically tailored for relevance to paid HCWs who provide services to clients living with dementia. The programme includes the following content: key information about dementia and its presentations and impact on daily living, practical strategies for effective communication with clients living with dementia and their family carers, person-centred care, understanding triggers for changed behaviours and effective responses, as well as strategies for staff self-care.

The programme was originally designed as a face-to-face training program. In response to government guidelines and restrictions due to the COVID-19 pandemic, PITCH training has also been adapted for online delivery. The face-to-face programme is conducted as two half-day workshops (total length is 7 h including breaks), and the online programme is delivered across three 2-h sessions (total 6 h), with similar programme content across the two modes of delivery. In the training, HCWs are provided with a workbook and encouraged to actively participate in group discussion through case studies and role modelling to provide experiential learning. During the trial, HCWs will be able to attend the PITCH training and complete the outcome measures at all periods as part of their work time, with backfilling of their shift funded by the study. HCWs attendance will be noted by the research team and reported back to site managers. In discussion with site managers, training sessions will be scheduled to maximise HCW attendance. Managers will promote the sessions and encourage attendance, though PITCH training will not be compulsory. Implementing PITCH will not require alteration to usual care pathways for dementia care and these will continue for both trial arms.

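### Time to transition from home is grouped by training received, with no stated handling of crossover or clustering, in a design where every cluster is eventually trained

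*Protocol article*

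**What the plan says.** Under Statistics and data analysis, time to all-cause transition from home is analysed by survival methods, "employing Cox proportional hazards modelling and Kaplan-Meier survival curves", followed by the comparison rule "Clients of HCWs who did and did not receive PITCH training will be compared using Log rank tests". The article gives no time origin, no censoring at crossover and no time-varying exposure for this outcome. Intention-to-treat appears in that section only in connection with missing data. Random effects for cluster and participant are attached to the mixed models for the scale outcomes; the survival sentences name no cluster term.

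Three other statements bear on the rule:

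- Trial design: "Every cluster begins in the control condition and eventually receives the intervention, with crossover determined randomly".
- Abstract, Methods: the intervention group is trained "after baseline measures", and "The control group receives PITCH training 6 months after baseline measures".
- Intervention Procedures: managers encourage attendance, "though PITCH training will not be compulsory".

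The Trial design section words the timing differently: "the intervention groups that receive PITCH training at period 2 or the control groups that receives PITCH training at period 3", where periods 2 and 3 are labelled 6 and 12 months. The fourth hypothesis sets usual-care clients against clients of PITCH-trained HCWs on days before leaving home, with no time horizon. The outcome itself is listed under Other outcomes.

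**The concern.** Whether a client's HCWs received training is known only after randomisation, and in this design it depends on how long the client stays at home. On the Abstract's timing, a control-cluster client still at home at 6 months passes into the trained group if the HCWs attend. One who leaves earlier can never do so. Used as a fixed label from baseline, training received credits the trained group with event-free time that was needed to enter it. Voluntary attendance adds a second departure from the randomised comparison.

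At stake is the hypothesis on days before leaving home. One way of carrying out the sentence could show a large benefit from a programme with no effect. Another would understate a real effect. Neither deals with the correlation of clients within clusters.

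**Working it through.** **Inputs from the article.** About 108 clients (Sample size); 12 months of follow-up; training after baseline for intervention clusters and at 6 months for control clusters (Abstract). The article gives no event count, hazard ratio or power for this outcome, so there is no planned figure to reproduce.

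**Assumptions.** 54 clients per arm; exponential times; training at month 0 or month 6; 12-month transition rate p of 10-40%; no cluster or calendar effect unless stated. Each scenario had 1,000 replicates, tested at two-sided 5%.

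**1. Size of the untrained group, fixed ever/never label, full attendance.** Expected number = 54 × (1 − (1 − p)^0.5). For p = 20% this is 54 × (1 − 0.894) = 5.7. All of these clients have the event.

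**2. Behaviour with no true effect (HR = 1).** Cells give the rejection rate, then the median HR.

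| p | Untrained: formula / simulated | Ever vs never trained | Arm, 12 months | Arm, censored at month 6 |
|---|---|---|---|---|
| 10% | 2.8 / 2.8 | 1.000; 0.010 | 0.045; 0.997 | 0.038; 0.997 |
| 20% | 5.7 / 5.7 | 1.000; 0.024 | 0.048; 1.018 | 0.051; 0.999 |
| 30% | 8.8 / 8.9 | 1.000; 0.039 | 0.042; 0.997 | 0.054; 1.002 |
| 40% | 12.2 / 12.2 | 1.000; 0.055 | 0.053; 1.006 | 0.060; 1.018 |

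Replicates with an empty untrained group give no test and are left out. At p = 10% their expected share is 0.9^27 = 0.058. A separate simulation with 18 clusters of 6 clients gave 98-100% rejection and HRs of 0.03-0.08 at rates of 15-35%.

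**3. Imperfect attendance.** Suppose 20% of clients have HCWs who are never trained. At p = 20% the untrained group is 0.2 × 108 + 0.8 × 54 × (1 − 0.8^0.5) = 21.6 + 4.6 = 26.2. Many of these clients stay at home, which weakens the bias: rejection is 0.578 with HR 0.384. At p = 30% rejection is 0.755 with HR 0.377.

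**4. Randomised arm over 12 months, true HR 0.70.** After month 6 both arms are trained, so the contrast there is nil. Events fall roughly as 1 + 0.7 = 1.7 before month 6 and 0.7 + 0.7 = 1.4 after it. The early weight is 1.7 / 3.1 = 0.548, and exp(0.548 × ln 0.70) = 0.82. Simulated medians were 0.809 (p = 20%) and 0.815 (p = 30%); the separate simulation gave 0.79. Censoring at month 6, or time-varying training status, gave 0.670 and 0.693. With full attendance these two analyses coincide, because after month 6 nobody in the risk set is untrained.

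**5. Clustering.** With an assumed cluster log-frailty variance of 0.2 or 0.4, an unadjusted log-rank test by sequence rejected a true null in 7% or 10% of trials. The exact values move with the assumed event rate.

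**6. Alternative timing.** If the Trial design wording means training at months 6 and 12, the ever/never label still rejects in every replicate. Early leavers in both arms then count as untrained, and the interval with a randomised contrast moves to months 6-12.

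**The case against.** The strongest reply is that the sentence need not mean a fixed ever/never label. The article's hypotheses use similar language, clients of trained against untrained HCWs, for the trial's treatment contrast, so the sentence may be shorthand for the randomised arms. It could also describe time-varying status in the Cox model named just before it. Both keep type I error near 5% before clustering. This stands. A reader might infer that the result is bound to be biased in favour of PITCH, and the article does not support that, because it never fixes the label over the whole of follow-up.

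Three further corrections stand. A reader might infer that every early leaver counts as untrained; on the Abstract's timing this applies in control clusters only (and to clients of non-attending HCWs), since early leavers in intervention clusters count as trained. The 98-100% figure needs full attendance, which the voluntary training makes doubtful. And the outcome is neither primary nor listed as secondary.

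It can also be said that frailty terms, robust errors and censoring rules belong in an analysis plan that is not shown. That is fair as to their absence. It does not excuse the rule that is stated: grouping by training received, tested with a log-rank test, in a cluster-randomised trial where all clusters cross over. The arm reading does not rescue it, because months 6-12 then have no usual-care comparator.

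**Conclusion.** The concern holds in a conditional form. As worded, the comparison groups clients by a post-randomisation fact and leaves crossover open. Its size depends on how the sentence is carried out:

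- **Fixed ever/never label:** a spurious benefit under no effect, with rejection from 58% (20% of clients with never-trained HCWs) to about 100% (full attendance).
- **Randomised arm over 12 months:** near-nominal error before clustering, but a true HR of 0.70 appears as about 0.8.
- **Any reading with a plain log-rank test:** clustering is ignored, with 7-10% null rejection at the assumed frailty variances.

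Event rates, attendance and frailty variances are assumptions, as the article supplies none. Severity is moderate: the SCIDS analysis is untouched, but a stated hypothesis rests on this comparison.

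**What to change.** Replace the log-rank sentence with a rule of this kind: clients are compared by the randomised sequence of their cluster, regardless of HCW attendance, over the interval when one sequence is allocated to training and the other is not, with censoring at the control clusters' allocated crossover. Alternatively, fit a Cox model in which cluster-level training status is a time-varying covariate that switches at the allocated crossover date. In either case use shared frailty or cluster-robust standard errors, and replace the plain log-rank test with a cluster-adjusted one.

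Reconcile the training times in the Abstract (after baseline; 6 months) with those in Trial design (period 2; period 3), so that the crossover date and the comparison interval are fixed. Until that is done, no particular censoring month can be written in.

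The cost is wording and a few lines of code, with no new data. The downside is that events after control crossover do not add to the main contrast. In the simulations this did not cost power: with a true HR of 0.70, rejection was 0.082 and 0.106 when censored at crossover, against 0.061 and 0.083 by arm over 12 months (rates 20% and 30%, before clustering). Power is low either way, and the report should say so.
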